## Abstract

**Background:**

Tracheostomy is one of the most frequent techniques in intensive care units (ICU). Fiberoptic bronchoscopy (FB) is a safety measure when performing a percutaneous dilatational tracheostomy (PDT), but the controversy surrounding the routine use of FB as part of the procedure remains open. National surveys in some European countries showed that the use of FB is non-standardized. Retrospective studies have not shown a significant difference in complications between procedures performed with or without a bronchoscope. International guidelines have not been able to establish recommendations regarding the use of FB in PDT due to lack of evidence.

**Design:**

This is a multicenter (three centers at the time of  publishing this paper) randomized controlled clinical trial to examine the safety of percutaneous tracheostomy using FB. We will include all consecutive adult patients admitted to the ICU in whom percutaneous tracheostomy for prolonged mechanical ventilation is indicated and with no exclusion criteria for using FB. Eligible patients will be randomly assigned to receive blind PDT or PDT under endoscopic guidance. All procedures will be performed by experienced intensivists in PDT and FB. A Data Safety and Monitoring Board (DSMB) will monitor the trial. The primary outcome is the incidence of perioperative complications.

**Discussion:**

FB is a safe technique when performing PDT although its use is not universally accepted in all ICUs as a routine practice. Should PDT be monitored routinely with endoscopic guidance? This study will assess the role of FB monitoring during PDT.

**Trial registration:**

ClinicalTrials.gov NCT04265625. Registered on February 11, 2020

**Supplementary Information:**

The online version contains supplementary material available at 10.1186/s13063-021-05370-x.

## Background

Tracheostomy is one of the most frequently performed techniques in intensive care units (ICUs). The era of modern tracheostomy has a starting point in 1909 when Chevalier Jackson [1] describes the surgical tracheostomy. In 1985, Ciaglia et al. [2] described the percutaneous dilatational tracheostomy (PDT) that met the requirements of simplicity, swiftness, and safety, which, along with the possibility of being performed at the bedside, developed a new way of understanding surgical airway access in the critically ill patient. Subsequently, changes [3–5] over the classical technique and other modalities were developed [6–8].

A few years after the description of PDT, Paul et al. [9] performed tracheostomies using endoscopic guidance in four patients, on the basis that the blind nature of PDT justified most of the complications associated with it. The duration of the procedure in all four patients lasted between 10 and 15 min, and the authors stated that the use of endoscopic guidance prevented damage to the posterior tracheal wall and helped in identifying the puncture site thanks to transillumination. Currently, the “routine” use of endoscopic guidance as part of percutaneous tracheostomy is controversial [10–13] and guidelines cannot establish recommendation levels [14–16].

We postulate that percutaneous tracheostomy performed under endoscopic control does not reduce the incidence of perioperative complications of the procedure in critically ill patients when it is performed by experienced physicians in patients without anatomical abnormalities.

## Methods/design

### Justification of the study

Besides a few recommendations that have been made regarding some modalities [4, 5, 8], endoscopic guide as part of PDT is a controversial issue. Some authors suggest that it is a safety measure that can prevent serious complications and should be considered in all PDT procedures in the absence of contraindications [17–19]. For others [10], these studies are limited and unclear whether visualization of the interior of the airway is a necessary component of the procedure. In two comparative retrospective studies [10, 11], the addition of bronchoscopy was not accompanied by a significant difference in complications between procedures performed with and without a bronchoscope. In a retrospective analysis [12] involving trauma patients, the use of fiberoptic bronchoscopy (FB) when performing PDT was not routinely required but might be used as an important adjunct in selected patients. In a retrospective review [13] of 3162 PDT, the largest reported series percutaneous tracheostomy in critically ill patients, the authors conclude that routine bronchoscopic guidance is not necessary.

The advantages of using a FB are the ability to transilluminate the neck and directly visualize the trachea during needle insertion and dilation. In patients with difficult airways or altered anatomy, the bronchoscope allows for repositioning of the needle to avoid puncturing surrounding structures [20]. FB is a safety measure when performing PDT, although its use in mechanically ventilated patients could be associated with some risks (i.e., auto-PEEP [21], significant hypercarbia [22]). In addition, the bronchoscope may increase the procedure time and costs [10].

It has been suggested [23, 24] that bronchoscopy should be used by surgeons who are less skilled with PDT, as a method to reduce complications or in case of anatomical challenge [25]. FEPIMCTI [14] guidelines do not establish recommendations regarding this technique because there is insufficient evidence to suggest that using a bronchoscope while performing PDT reduces the rate of complications. The French Society of Intensive Care [15] guidelines established a weak recommendation based on a study in 60 patients in which endoscopic guidance was associated with fewer minor complications. The Indian Society of Critical Care Medicine expert panel states that fiberoptic bronchoscope may be used, whenever available to aid PDT although it does not reduce the rate of complications [16].

Currently, evidence regarding the use of FB in PDT is practically non-existent. Large prospective randomized studies are needed comparing PDT with and without FB, performed by experienced personnel in both the PDT technique and the endoscopic guidance. This rationale is the basis and justification for the present study.

The aim of this study is to assess the occurrence of perioperative complications associated with the procedure of percutaneous tracheostomy under endoscopic guidance versus blind percutaneous tracheostomy.

### Study design

#### Design

This is a randomized, controlled, multicenter clinical trial (three centers at the time of publishing this paper, Hospital Universitario La Paz, Hospital Universitario Rey Juan Carlos and Hospital Universitario Infanta Leonor in Madrid, Spain). The trial was designed in accordance with the Declaration of Helsinki, the Convention of the European Council related to human rights and biomedicine, and within the requirements established by Spanish legislation in the field of biomedical research, the protection of personal data and bioethics. The trial was registered on the 11th of February 2020 at http://www.clinicaltrials.gov with identification no. NCT 04265625. The study protocol (Version 1, 11th October 2019) was approved by the Ethics Committee (Hospital Universitario La Paz, Madrid, Spain, identification no. 5455 -Additional file 1) and by the Institutional Review Board of Hospital Universitario Rey Juan Carlos and Hospital Universitario Infanta Leonor, Madrid, Spain. For inclusion into the study, approval on a written informed consent will be requested by the local investigators from the patient’s relatives or legal representatives (Additional file 2). Our protocol followed the SPIRIT (Standard Protocol Items: Recommendations for Interventional Trials) guidelines. See Additional file 3 for the SPIRIT checklist of the study protocol.

#### Study population

We will include patients admitted to the ICU requiring percutaneous tracheostomy for prolonged mechanical ventilation. Inclusion criteria are (i) hospitalized adults of ≥ 18 years at the time of screening, and (ii) subjects (or a legal representative, or the nearest relative, or a relative by marriage, as appropriate) provide signed informed consent prior to initiation of any study procedures. We will exclude the following patients: (i) patients with increased intracranial pressure (ICP), either suspected or observed by its monitoring; (ii) patients who have any absolute or relative contraindications [26] to the performance of PDT: morbid obesity, neck deformity, coagulopathy (INR> 1.5) or thrombopenia (platelet count <50,000) with difficulty in reversal, need to establish an emergency surgical airway, cervical spine injury, previous neck surgery or previous tracheostomy, surgical area infection and high oxygen requirements (FiO_2_ ≥ 0.7), and PEEP (> 10 cmH_2_O); and (iii) patients in whom, for safety reasons, the physician in charge considers that the procedure should be monitored with endoscopic guidance.

#### PDT modality used

PDT will be performed with the single dilatation method, as it is the usual practice in the ICU in La Paz University Hospital. For both arms, the patient will be placed with the neck extended and the usual aseptic measures will be taken in the surgical area. All patients will be monitored with electrocardiographic control, invasive blood pressure, and continuous pulse oximetry. A FiO_2_ of 100% will be maintained throughout the procedure with correct visualization of the curves and parameters obtained from the mechanical ventilator. Sedation and analgesia will be initiated, and if it is already being infused continuously due to its basal situation, an extra dose will be administered if necessary along with a bolus dose of a non-depolarising neuromuscular blocking agent (usually cisatracurium).

#### Randomization

Candidate patients will be randomized with a 1:1 ratio. Randomization will be performed with the sealed envelope system. Patients randomized to the “PDT with endoscopic guidance” arm will undergo the procedure controlled with a fiberoptic bronchoscope (as is usual clinical practice when dealing with patients with anatomical challenges or difficult airways). The bronchoscope will be introduced through the endotracheal tube (ETT), and under fibroscopic vision, ETT will be placed in such a way that the balloon is just below the vocal cords. To minimize the adverse effects that can be derived from the use of the fiberoptic bronchoscope, the difference between the internal diameter of the ETT and the external diameter of the bronchoscope will be at least 2 mm [21]. In patients randomized to the “PDT without endoscopic guidance” group, ETT will be placed with the balloon under the vocal cords under direct laryngoscopy vision, as it is the usual practice when dealing with patients without difficult airway or anatomical challenge.

#### Percutaneous tracheostomy technique with a single dilator

Once the patient and the surgical field are prepared, anatomical structures (cricoid cartilage, cricothyroid membrane, and tracheal rings) are identified by palpation, and subsequently, an incision (preferably horizontal) is made in the skin of approximately 1.5–2 cm above the point where the tracheal puncture will be performed, followed by a blunt dissection of soft tissues in order to easily locate the tracheal structures. A tracheal puncture will be performed via the incision, preferably between the first and second tracheal ring. After confirming the location in the tracheal lumen by air aspiration (or direct vision with fiberoptic bronchoscope in patients randomized to this arm), the needle and syringe are withdrawn, leaving the tracheal sheath in the tracheal lumen through which the J-shaped metal guide will be inserted. Subsequently, the sheath is removed and the first dilatation is carried out through the metal guide with the small 14Fr dilator. Then, definitive dilatation will be performed with the Teflon catheter that has been previously built into the curved dilator with the hydrophilic covering. This curved dilator has to be moistened with physiological saline solution prior to its introduction to soften the structure. Subsequently, it is introduced through the metal guide through the soft tissues into the tracheal lumen (up to the external signal of 38Fr). Once this maximum, dilation has been achieved, the curved dilator is extracted, and the tracheostomy cannula along with the cannula introducer is advanced over the metal guide and the Teflon catheter into the tracheal lumen. Once the tracheostomy cannula has been introduced, the cannula introducer, the Teflon catheter, and the metal guide are removed (along with the fiberoptic bronchoscope in patients randomized to this arm). Finally, secretions are aspirated, the tracheal cannula balloon is inflated, and the patient is connected to the ventilator.

#### Level of experience of the personnel involved in the technique

Percutaneous tracheostomy has been performed at the coordinator center since 1991 [27], and during many years, it was done without bronchoscopy. Over time, with the addition of other faculty, and as an adjunct in residency training, the use of FB was added to the procedure (although no routinely). Physicians of participating centers are highly experienced in PT and the use of FB. Therefore, the procedure will be performed by experienced personnel and those procedures performed by physicians in the learning curve (i.e., residents), it will be directly supervised by experienced intensivists [5].

#### Data collection

In addition to demographic variables, and duration of the procedure (from skin incision to placement of tracheostomy tube), we will collect perioperative complications (following the classification proposed by Durbin [28] modified [29]. Minor complications include those that are easily corrected, with no risk of sequelae or need of unscheduled therapeutic strategies for their solution: (a) haemorrhage: bleeding controlled with digital pressure that does not cause hemodynamic instability, nor requires surgical revision or transfusion; (b) transient desaturation: desaturation during the procedure (SpO_2_<90% but ≥ 85%); (c) loss of airway control: failure to secure the airway without impact on SpO_2_ (not <90%); (d) atelectasis: partial atelectasis (segmental or lobar) without a decrease in SpO_2_<90% and that does not require fiberoptic bronchoscopy for its resolution; (e) arterial hypotension, which requires expansion with less than 1000 ml of fluids and does not require administration or increase of previous doses of inotropics; (f) barotrauma: subcutaneous emphysema; (g) rupture of tracheal rings: rupture of the tracheal ring during any phase of the procedure (only in patients in whom endoscopic guidance is performed); and (h) technical problems without clinical repercussions: puncture of the ETT cuff, difficulty in inserting the cannula or impossibility to complete the technique as an isolated complication that did not lead to repercussions such as desaturation or loss of the airway. Major complications include those when an unscheduled therapeutic act was required, or when the complication entails potential risk (although there had been no life threat or consequential sequelae), or there is a real risk to life, cardiac arrest, or death directly related to the complication derived from the technique: (a) hemorrhage: bleeding that causes hemodynamic instability, and/or requires surgical revision, and/or transfusion; (b) desaturation (SpO_2_<85%) of any duration; (c) loss of airway control causing a drop in SpO_2_<85%; (d) total or partial atelectasis that have an impact on SpO_2_ or require a therapeutic maneuver for its solution (fiberoptic bronchoscopy); (e) hypotension that requires treatment with more than 1000 cc of fluids, and/or initiation of vasopressors, or an increase in previous doses; (f) false passage that causes injury to the trachea or mediastinal emphysema or desaturation (SpO_2_ <85%); (g) barotrauma: pneumothorax or mediastinal emphysema; (h) rupture or tear of the tracheal wall; (i) injury to the posterior wall of the trachea: damage produced to the posterior wall of the trachea with the needle, guide, or dilator; and (j) technical problems with clinical repercussions: puncture of the ETT cuff, difficulty in inserting the cannula, or impossibility of completion of the technique that entails consequences such as desaturation or loss of the airway or serious complications that require a change in strategy.

We will also collect the arterial partial pressure of CO_2_ at the beginning and end of the procedure, the arterial partial pressure of O_2_ at the beginning and end of the procedure, pH at the beginning and end of the procedure, minimum arterial oxygen saturation (measured by pulse oximetry) during the procedure, and maximum end-tidal CO_2_ during the procedure (if capnography is available).

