#### Statistical analysis plan

Data will be collected in each participating ICU using a standardized form. Then, data will be transmitted to the coordinating center whenever a patient dies or is discharged from the hospital. Before exporting the data into a computerized database at the randomization center, the coordinator ([name]) will check the completeness and the quality of information. Logical checks will be performed for missing data and to find inconsistencies. If necessary, the data collector will contact the investigator by phone to validate the data or reformat the data for entry into the database. Considering that the rate of complications described in published work in which PDT with FB was performed ranged between 3.7% and 16%, and those without FB (eliminating extreme values) ranged between 11% and 25%, for a confidence level of 95%, a statistical power of 80% and a potential loss of 10%, a sample size of 221 patients has been calculated for each arm. Collected data will be anonymized in compliance with the Spanish Law 3/2018, of December 5, on Data Protection and Guarantee of Digital Rights. The results of the quantitative variables will be expressed as mean and standard deviation when they fit a normal distribution curve evaluated with the test of Kolmogorov-Smirnoff. Data without a normal distribution will be expressed as median and interquartile range. Qualitative data will be expressed through its absolute frequency and percentage. The comparison between quantitative variables will be carried out using the Student’s t test or the Mann-Whitney test, depending on the distributions of the variables analyzed. The chi-squared test will be used to demonstrate differences between qualitative variables. No imputation will be made of the lost data. All tests will be considered two-tailed at a 95% level of significance. All statistical analyses will be performed using statistical software SAS Enterprise Guide 8.2 (Cary NC, SAS Institute Inc., USA). Statistical significance will be set at p<0.05.

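### Tracheal-ring rupture, a component of the primary outcome, can be scored only where the bronchoscope is used, which biases the comparison against bronchoscopy by an unknown amount

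*Protocol article*

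**What the plan says.** The Design paragraph of the protocol article's abstract states: "The primary outcome is the incidence of perioperative complications". The section Data collection says "we will collect perioperative complications" and then gives the article's only list of them: minor items (a) to (h) and major items (a) to (j).

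Minor item (g) reads "rupture of the tracheal ring during any phase of the procedure (only in patients in whom endoscopic guidance is performed". No other item in either list is limited to one kind of procedure. Major item (i), for example, is "injury to the posterior wall of the trachea: damage produced to the posterior wall of the trachea with the needle, guide, or dilator", with no restriction by arm.

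Endoscopic guidance is the randomized intervention, allocated 1:1 (Randomization). In the blind arm, entry into the trachea is confirmed by aspirating air (Percutaneous tracheostomy technique with a single dilator). The article describes no later airway inspection in that arm.

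The Background section states the hypothesis that endoscopic control does not lower the complication rate in experienced hands.

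**The concern.** A composite outcome can be compared between arms only if every component can be scored in both. Item (g) ties a component to the randomized treatment itself. It can turn an FB patient without other complications into a patient with an event, but cannot do the same for a patient who received the blind procedure.

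This adds to the recorded FB rate whatever the true effect of bronchoscopy. It makes a real benefit harder to show and can make two equally safe procedures look different. Because the shift favours the stated hypothesis, a result showing no FB benefit would be open to the criticism that the outcome definition helped to produce it. More patients do not help: the shift stays the same while the confidence interval narrows around it.

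**Working it through.** **Inputs from the article (Statistical analysis plan).** Published complication rates of 3.7% to 16% with FB and 11% to 25% without; two-sided 5% level; 80% power; 10% loss; chi-squared test; 221 patients per arm.

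**Step 1. The plan's own sample size.** The article does not say which pair of rates was used. The usual formula with pooled variance and no continuity correction is

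n = [1.960·√(2p̄(1−p̄)) + 0.842·√(p₁(1−p₁) + p₂(1−p₂))]² / (p₁ − p₂)²

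- 3.7% vs 11% (lower ends of both ranges), p̄ = 0.0735: (0.7233 + 0.3075)² / 0.073² = 199.4, so 200. Allowing for 10% loss, 200/0.9 gives 223 and 200 × 1.1 gives 220.
- 10% vs 20% (an assumed pair): (0.9897 + 0.4208)² / 0.10² = 199.0, so 199, and 199/0.9 = 221.1.
- Range midpoints (9.85% vs 18%) give 283, then 315 with loss. Upper ends (16% vs 25%) give 315, then 350. Neither fits.

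The figure of 221 is therefore reproduced closely by either of the first two pairs. Both are inferred. Evaluable patients per arm: 221 × 0.9 ≈ 199.

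**Step 2. Effect of item (g) on the recorded FB rate.** Let p be the FB-arm rate of all other complications and r the rate of ring rupture. The article gives no r, so 1%, 2% and 5% are assumed. If rupture is independent of the other complications, the recorded FB rate is p + (1 − p)·r. The blind-arm rate is left unchanged. At p = 11% the artificial excess is 0.89·r, that is 0.9, 1.8 or 4.5 percentage points, or about 1.8, 3.5 or 8.9 extra event patients among 199.

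**Step 3. Consequence for the test.** Exact enumeration of two independent binomials, 199 per arm, chi-squared test without continuity correction, two-sided 5%:

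| Scenario | r = 0 | r = 1% | r = 2% | r = 5% |
|---|---|---|---|---|
| No true difference, others 11% in both arms: chance of a false result that FB is worse | 2.4% | 4.5% | 7.7% | 25.7% |
| No true difference, others 18% in both arms: same | 2.5% | 4.1% | 6.2% | 17.5% |
| 3.7% vs 11%: power to show FB benefit | 82% | 67% | 50% | 13% |
| 10% vs 20%: power to show FB benefit | 81% | 72% | 62% | 31% |

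The r = 0 column is the position with item (g) out of the composite.

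**Step 4. If ruptures overlap with other complications.** Only a patient whose sole complication is ring rupture changes status. Suppose half of all ruptures occur in patients who already have another listed complication (an assumption). At p = 11% the recorded FB rate is then 11% + r/2: 12.0% for r = 2% and 13.5% for r = 5%. The false-worse probability becomes 4.9% instead of 7.7%, and 11.3% instead of 25.7%.

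**The case against.** The restriction has an obvious reason: a ring fracture is normally seen only through the bronchoscope, so it could not be recorded reliably in the blind arm. That explains the wording, but it also confirms that the component is measured unequally.

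The stronger objections concern size. The rupture rate is assumed; independence overstates the effect if ruptures occur in already complicated procedures; and the published 3.7% may already include ruptures seen by camera, in which case adding r on top counts them twice. All three stand. They limit what can be said about magnitude, not about the existence or direction of the bias. The unseen full protocol might confine the primary outcome to major complications, which would remove the problem, but nothing in the article does so.

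A reader might also infer more than the article supports:

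- *That a ring rupture in the blind arm always scores zero.* One with clinical effects can score as haemorrhage, subcutaneous emphysema, a technical problem, or the unrestricted major item for a tracheal wall tear. Only otherwise silent ruptures are lost.
- *That posterior-wall injury has the same defect.* Major item (i) carries no restriction by arm. Such lesions are plausibly easier to see with a bronchoscope, but that is a practical limit of detection, not a fault in the definition. FB might also truly prevent them.
- *That tying item (g) to the procedure performed makes the bias worse.* A blind-arm patient converted to FB could then score the item in the blind arm as randomized, which slightly reduces the bias.
- *That rupture rates near 10% should be considered.* The article puts all complications with FB at 3.7% to 16%, so 10% for one minor item is hard to reconcile with its own figures.

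**Conclusion.** The concern holds for item (g). As written, the primary outcome contains a component that can be scored essentially only under bronchoscopy. The bias is against FB, favours the stated hypothesis, and does not shrink with sample size.

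Its size cannot be established from the article. Under the assumed range, a rupture rate of 1% does modest harm to the error rate but already costs 9 to 15 points of power. At 2% the cost is 19 to 32 points, and at 5% most of the power is gone. These figures rest on independence, on 199 evaluable patients per arm, on inferred planning pairs, and on FB planning rates that exclude ring rupture. They are smaller where ruptures coincide with other complications. They do not show that a future null result would be due to detection alone, only that the two explanations could not be separated. The sample size of 221 per arm is not in question on this account.

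**What to change.** Amend the outcome definition, before outcomes are compared by arm, so that minor item (g) is not part of the primary composite. Report ring rupture descriptively for patients who had bronchoscopy.

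Keep the major items, including posterior-wall injury, in the primary outcome as defined. Making them count only when clinically manifest would drop potentially serious injuries from a safety outcome. Instead, add a sensitivity analysis that leaves out lesions seen only by bronchoscope, since these are also easier to detect in the FB arm. This requires recording how each airway lesion was found.

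The cost is slightly fewer events in the FB arm and a documented change to the primary outcome of a trial that has been enrolling since December 2019 (Trial status). The amendment should therefore be dated and should state that it was made without knowledge of results by arm. The sample size need not change for this reason.

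### Tracheal-ring rupture, one listed complication, is scored only where endoscopic guidance is performed, which biases the primary comparison against FB by an unknown amount

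*Protocol article*

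**What the plan says.** The Abstract (Design) states: "The primary outcome is the incidence of perioperative complications". It also gives the comparison: "Eligible patients will be randomly assigned to receive blind PDT or PDT under endoscopic guidance".

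The complications are defined under Data collection: "we will collect perioperative complications (following the classification proposed by Durbin [28] modified [29". The list that follows has 8 minor items, (a) to (h), and 10 major items, (a) to (j). Minor item (g) is "rupture of the tracheal ring during any phase of the procedure (only in patients in whom endoscopic guidance is performed"). No other item carries a restriction of this kind.

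The Background postulates that "percutaneous tracheostomy performed under endoscopic control does not reduce the incidence of perioperative complications" when experienced physicians treat patients without anatomical abnormalities.

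The Statistical analysis plan section cites published complication rates of 3.7% to 16% with FB and 11% to 25% without. It plans 221 patients per arm for 80% power after 10% loss. Tests are two-tailed, with chi-squared for qualitative variables.

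**The concern.** A fair comparison needs the same events to be countable in both arms. Here, whether one event can be counted depends on the intervention under test. Under the written rule, a ring rupture during a guided procedure is a complication, and the same rupture during a blind procedure is not. The sections on randomization and technique give blind-arm patients no airway inspection that would even things out.

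The rule can only add events among patients treated with FB. With good adherence those patients are the FB arm, so the error has a known direction: it hides a true benefit of FB or makes FB look worse when the arms are equal. That direction agrees with the stated hypothesis, so a result in line with it would be hard to defend. Neither randomization nor a larger sample removes the bias.

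The rule also follows guidance performed, not allocation. A blind-arm patient converted to FB becomes scorable, and an FB-arm patient treated without FB stops being so.

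**Working it through.** **Inputs from the article:** 221 per arm, 10% loss, two-sided 5% level, 80% power, 1:1 allocation, and the two ranges of published rates. Evaluable per arm: 221 × 0.9 = 198.9, taken as 199.

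**Reproducing 221.** The article does not name the two rates used. With the pooled-variance formula for two proportions,

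n = [1.96·√(2p̄(1−p̄)) + 0.84·√(p₁(1−p₁) + p₀(1−p₀))]² / (p₁−p₀)²,

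two pairs inside the stated ranges fit:

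- 10% versus 20%: n = 199.0; divided by 0.9 this is 221.1.
- 3.7% versus 11% (the lower limits of both ranges): n = 199.4; divided by 0.9 this is 221.6.

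Both are used below.

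**Adding the FB-only item.** Let p be the FB-arm rate of the items that can be scored in either arm. Let r be the share of otherwise complication-free FB patients with a ring rupture. The documents give no value for r, so it is an assumption and is varied. The observed FB rate is

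p_FB = 1 − (1−p)(1−r) = p + r(1−p).

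The blind-arm rate p₀ is unchanged. The added bias is r(1−p). For p = 3.7% this is 0.963 × 1% ≈ 1.0 point at r = 1%, and 0.963 × 5% ≈ 4.8 points at r = 5%, against a planned difference of 11 − 3.7 = 7.3 points. That difference is used up at r = 7.3/0.963 ≈ 7.6%, expressed as a percentage.

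**Power.** With d = p₀ − p_FB, the probability of a significant result in favour of FB is Φ[(d − 1.96·SE₀)/SE₁]. SE₀ is the pooled and SE₁ the unpooled standard error at 199 per arm. The probability of a significant result against FB has −d in place of d.

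Worked case, 10% versus 20% with r = 3%:

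- p_FB = 1 − 0.90 × 0.97 = 12.7%, so d = 7.3 points.
- p̄ = 16.35%, SE₀ = 0.0371 and SE₁ = 0.0369.
- (0.073 − 1.96 × 0.0371)/0.0369 ≈ 0.01, which gives power of 50%.

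| r | Power, 10% v 20% | Power, 3.7% v 11% | Significant against FB, true rate 11% in both arms |
|---|---|---|---|
| 0 | 80% | 80% | 2.5% |
| 0.25% | 78% | 77% | 2.9% |
| 0.5% | 76% | 73% | 3.4% |
| 1% | 71% | 65% | 4.6% |
| 3% | 50% | 34% | 12.5% |
| 5% | 31% | 13% | 26% |

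The r = 5% row is an extreme for the low planning pair: isolated ring rupture would then be 4.8 of 8.5 points, more than half of all FB-arm events.

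**The case against.** **Ring rupture can be seen only by endoscopy, so the parenthesis is an honest note.** This probably explains the rule. It does not justify counting the item in a between-arm comparison, because an event visible in one arm only cannot contribute fairly to a difference.

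**The article never says that a single minor item makes a primary event.** True. Data collection lists items to be collected, and if only major complications counted, item (g) would not touch the primary outcome. But the same term covers minor and major items together under Data collection and names the primary outcome in the Abstract, and nothing limits that outcome to major events. Inclusion is the plain reading, though not an explicit statement.

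**The effect may be small.** This stands. Only isolated ruptures matter for a patient-level outcome, so the effective r may be well below 1%, where the loss of power is a few points. Serious tracheal injury (false passage with injury, wall rupture or tear, posterior-wall damage) is listed as major without any restriction.

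**Part of the power loss may be counted twice.** This also stands. The published FB rates may already include ruptures seen at bronchoscopy, and the article does not say. If they do, the loss against planned power is smaller. The asymmetry and the error when the arms are truly equal remain.

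**Stronger readings.** A reader might infer that the arms are compared on wholly different endpoints, or that nothing in the blind arm can offset the extra events. The documents do not support either: 17 of the 18 items have no such restriction, and a blind-arm patient converted to FB becomes scorable, which dilutes the bias. Nor do they support a claim that the trial will wrongly find FB harmful, since that depends on an unstated rate.

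**Conclusion.** The point holds as to existence and direction. As written, one minor item out of 18 can add events only among FB-treated patients, which tilts the primary comparison against FB and towards the article's hypothesis. Crossover would weaken the tilt without removing its cause.

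The size cannot be fixed from the documents. Over the assumed range of 0.25% to 5%, the effect runs from a loss of about 2 to 3 points of power to the loss of most of it, and from a negligible to a roughly tenfold rise in the chance of a significant result against FB (2.5% to 26%). These figures rest on three assumptions: the primary outcome is any listed complication per patient, 199 patients per arm are evaluable, and the planning rates exclude ring rupture.

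The case for correction rests mainly on the one-sided definition and the low cost of removing it, and does not need any single value of r.

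**What to change.** State that minor item (g) is not part of the primary outcome in either arm, so that a patient whose only event is (g) has no primary-outcome complication. Continue to record ring rupture and report it descriptively for patients who had FB. Give the version with all items as a labelled sensitivity analysis.

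The cost is one sentence in the outcome definition, with no extra patients. There are two downsides. One minor item leaves the primary outcome. And the definition changes during enrolment, since the Trial status section dates the first patient to December 2019. The change should therefore be documented as an amendment made before any comparison by arm.

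It can be applied to patients already enrolled if the form records each item separately. The article mentions only a standardized form, so this must be confirmed.
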